### Qualitative data

The in-depth interview will be conducted with mothers to understand their expression, fill gaps in knowledge or to identify contextual factors that influenced impact of GPC. For this purposes, at least 6–8 in-depth interviews will be conducted in the study sites, however, actual number will be determined based on data saturation against explored board themes. In-depth interviews will be carried out by using flexible guideline. After consent, all interviews will be recorded by using digital recorder.

## Outcome of the study

### Primary outcome

Primary outcomes will include ANC and PNC coverage, skilled birth attendance and institutional deliveries, low birth weight (<2500 g), preterm birth, caesarean delivery, postpartum complications and breastfeeding rate (2 months postpartum). It is expected that due to GPC some outcome variables like ANC, PNC, skilled birth attendance, institutional deliveries and breastfeeding rate will be improved.

### Secondary outcomes

Some secondary outcomes like pregnancy induced hypertension, infant admission to hospital and perinatal death will be documented for both groups.

## Data analysis

The analysis of quantitative data will be based on a before and after assessment of the selected indicators, calculation of changes, and statistical significance based on 95% confidence intervals and other standard significance tests. Independent sample *t*-test for mean and proportion will be performed to test significance of difference in outcome variables between intervention and comparison group. To examine the normality of continuous outcome variable (like, low-birth-weight) histogram will be drawn. If the outcome variable found non-normally distributed, non-parametric test method (like, Kruskal–Wallis) will be employed. Advanced statistical techniques (such as multivariate regression analyses), will be used to document the net effects of the interventions on the outcome indicators after controlling for the individual-level socioeconomic factors. Data analysis will be done by using STATA 13.0.

For qualitative data analysis, content analysis will be done manually with qualitative information obtained through in-depth interviews. Immediate after the interview, the interviewers will complete the field-notes and transcribe the recording. After transcribing the interview, they will read the transcript carefully to identify potential themes. After then coding of data will begin through identifying possible themes and sub-themes.

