## Research design and methods

The study is quasi-experimental in design. The participants who are joining the GPC will be compared with those who receive standard individual prenatal care. Those who are will join the intervention program considered as “intervention group”. On the contrary, ‘comparison group’ are those who do not join this intervention. The intervention group will receive group prenatal care, and the comparison group will receive existing individual prenatal care as provided by the facilities following guidelines recommended by the Ministry of Health and Family Welfare (MOHFW), Government of the People’s Republic of Bangladesh.

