### Inclusion criteria for participants

Potential participants for either group are to be pregnant women with less than 20 weeks of gestational age, between the age of 18 and 42, without medical complications like pregnancy with jaundice, heart disease, asthma, diabetes, and willing to participate in this study.

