## Randomization

Participants are randomly assigned to the intervention and comparison groups. After meeting the inclusion criterion and obtaining informed consent block randomization is used. Computer-generated random numbers is assigned which have been pre-assigned to one of the two groups (intervention and comparison). The random numbers corresponding to either group has been sealed in an envelope numbered sequentially. The sealed envelope is opened after obtaining the informed consent. Until opening of the envelope, neither the participants nor the healthcare provider is aware of the group that they are assigned to. The envelope that contained “A” meaning “Intervention group” and the envelope contained “B” meaning “Comparison group”.

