### Formation of group for the intervention

Each group consisted of 6 to 10 women. They met 4 to 6 times throughout the pregnancy period. Groups were formed considering the gestational age of the women. Each session continue up to two hours. The entire GPC sessions are held in separate rooms with presence of pregnant mothers of intervention group. It can reduce the likelihood of mixing with other pregnant mothers.

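### The adjusted analysis names socioeconomic covariates but not gestational age at enrolment: under randomization this forgoes a small precision gain and causes no bias

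*Protocol article*

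**What the plan says.** The Data analysis section of the protocol article plans two between-group analyses. The first is unadjusted: "Independent sample *t*-test for mean and proportion will be performed to test significance of difference in outcome variables between intervention and comparison group". The second is a multivariate regression, which "will be used to document the net effects of the interventions on the outcome indicators after controlling for the individual-level socioeconomic factors". No obstetric or clinical covariate is named.

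Three other sections bear on the point:

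- Inclusion criteria for participants admits "pregnant women with less than 20 weeks of gestational age, between the age of 18 and 42", so gestational age has to be established for each woman, in both arms, at screening.
- Randomization places allocation after that check: "After meeting the inclusion criterion and obtaining informed consent block randomization is used". It mentions no stratification by gestational age.
- Formation of group for the intervention uses the same variable in the intervention arm: "Groups were formed considering the gestational age of the women".

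Antenatal coverage and preterm birth are both among the primary outcomes: "Primary outcomes will include ANC and PNC coverage, skilled birth attendance and institutional deliveries, low birth weight (<2500 g), preterm birth" and others.

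**The concern.** As the article stands, neither the allocation nor the analysis makes use of gestational age at entry. A woman who enters at 8 weeks has more of her pregnancy left for antenatal visits than one who enters at 19 weeks. Women are approached at booking or registration, so entry week also reflects how early a woman seeks care. It is therefore a plausible predictor of completing the standard number of visits. It is plausibly related to observed preterm birth as well.

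Leaving out a prognostic baseline variable in a randomized comparison has two costs. The treatment effect is estimated with more residual variance than necessary. Any chance difference in entry time between the arms also passes into the estimate. Both are avoidable with a variable the trial has to establish anyway.

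**Working it through.** **1. The plan's own figure.** Table 1 gives 202 per group for antenatal care, with 55% changing by 14 points (55% against 69%), 5% error and 80% power. Two-sided, with mean proportion 0.62:

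- Without continuity correction: n' = [1.96 × √(2 × 0.62 × 0.38) + 0.8416 × √(0.55 × 0.45 + 0.69 × 0.31)]² / 0.14² = 187.5, rounded up to 188.
- With continuity correction: n = (n'/4) × [1 + √(1 + 4/(n' × 0.14))]² = 201.5, rounded up to 202. This matches the table.

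The other seven rows of Table 1 reproduce exactly in the same way. The calculation uses unadjusted proportions, so the covariate set has no effect on it. The trial is sized on breastfeeding: 250 × 1.15 = 287.5, or 288 per group. With 15% lost, 288 × 0.85 = 245 remain evaluable.

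**2. Variance explained by entry time (assumed inputs).** Assume entry is uniform over 6 to 20 weeks and the chance of reaching the standard number of visits falls linearly by a total of D over that range. Take the outcome variance at the tabulated 55%: 0.55 × 0.45 = 0.2475. Then R² = (D²/12)/0.2475, and the equivalent number per arm is 245/(1 − R²).

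| Assumed fall D | R² | Equivalent n per arm | Gain |
|---|---|---|---|
| 20 points | 0.013 | 248 | 3 |
| 30 points | 0.030 | 253 | 8 |
| 50 points | 0.084 | 268 | 23 |

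In the largest scenario the standard error falls by a factor of √(1 − 0.084) = 0.957, about 4%.

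**3. Chance imbalance.** The SD of entry week is 14/√12 = 4.04. The 95% limit for the difference in arm means is 1.96 × 4.04 × √(2/245) = 0.72 week. The slopes are 20/14 = 1.4, 30/14 = 2.1 and 50/14 = 3.6 points per week. An imbalance at that limit would move the antenatal difference by 1.0, 1.5 or 2.6 points, against a planned 14.

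**4. If the outcome is rare.** Background describes the 55% as antenatal care from a trained provider, not completion of a standard number of visits. Study site gives 7% for a fourth visit locally. With a 7% mean, a linear fall cannot exceed 14 points (14% down to 0%). Then R² is at most (0.14²/12)/(0.07 × 0.93) = 0.025. The slope is 14/14 = 1 point per week, so the limiting shift is about 0.7 point.

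**5. Power for antenatal care, 55% against 69%, 245 per arm.** These figures use the normal approximation without continuity correction. Unadjusted power is 89.4%. For an assumed correlation r between entry week and outcome, the variance is multiplied by 1 − r²:

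| r | Variance factor | Power |
|---|---|---|
| 0.1 | 0.99 | 89.6% |
| 0.2 | 0.96 | 90.5% |
| 0.3 | 0.91 | 91.9% |
| 0.4 | 0.84 | 93.8% |

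The scenarios in step 2 correspond to r = √R² of about 0.12, 0.17 and 0.29, so the first three rows are the relevant ones.

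**6. Simulation check.** 1,500 trials were simulated with 245 per arm, entry uniform over 8 to 20 weeks and a true difference of 14 points. With a fall of 2 points per week, the standard error went from 0.0438 unadjusted to 0.0436 adjusted. With 4 points per week it went from 0.0449 to 0.0428. The mean estimate was about 0.138 with and without adjustment, so there was no bias either way.

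**The case against.** The case against has several parts.

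- **The list is not closed.** The article does not say that socioeconomic factors are the sole covariates, and a journal article may leave the full list to an analysis plan that is not shown. This stands as a limit: one cannot infer that gestational age has been excluded. The article does, however, state an adjustment set, and that set lacks an evident baseline candidate.
- **Nothing is biased.** A reader might infer that balance between the arms is lost. The Randomization section does not support that: entry time is balanced in expectation. The ordinary confidence interval already allows for chance imbalance. For antenatal care the standard error is √[(0.2475 + 0.2139)/245] = 4.3 points, or about ±8.5 points, which is far wider than the shifts of 1.0 to 2.6 points. This stands in full.
- **The mechanism is modest and narrow.** Entry before 20 weeks leaves about half the pregnancy, and no figure shows that later entrants cannot reach the standard number. The argument about remaining visits applies to antenatal care. It does not carry over to postnatal care, place of delivery or breastfeeding. Nothing in the documents makes maternal age prognostic. This also stands.
- **Group formation.** Sorting intervention women into groups by gestational age might be read as a bias in its own right. It is not: it does not alter which arm a woman was allocated to.

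There is a point on the other side. Research design and methods says "The study is quasi-experimental in design" and describes the arms by who joins, which conflicts with the Randomization section. If joining decided the arms, entry time could be a confounder and its omission more serious. That contradiction is a separate matter to be resolved. The present point does not depend on it, since adjustment is sensible under either description.

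**Conclusion.** The point holds as a minor one. The article names socioeconomic covariates and does not name gestational age at enrolment, a baseline variable that eligibility makes available in both arms and that is plausibly prognostic for antenatal visits and preterm birth. Under randomization the cost is precision and unadjusted chance imbalance, not bias.

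The size depends on inputs that the documents do not give. Assumed falls of 20 to 50 points over a uniform 6 to 20 weeks give about 1% to 8% of the antenatal outcome variance. If the local 7% figure described the outcome, the ceiling would be about 2.5%. No size has been worked out for preterm birth, where the link is a matter of plausibility. The stated sample size and power do not change, and no planned conclusion is put at risk.

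**What to change.** In Data analysis, add gestational age at enrolment (continuous) to the pre-specified covariates beside the socioeconomic factors, at least for antenatal coverage and preterm birth. Maternal age may be added but is not essential. Use the value established at the eligibility check, not one recalculated from gestational age at birth.

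Report the adjusted effect as a risk difference, so that it matches the differences in Table 1. If a logistic model is fitted, obtain the risk difference by standardising its predictions over all women. The adjusted odds ratio is a conditional measure, and the precision gain shown here does not carry over to it directly.

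The cost is one or two sentences and a stated effect scale. No new data are needed, provided the week of gestation was stored at screening. The article implies this but does not say it, so it should be confirmed. The Sample size section says that data collection is under way, so the change should be dated before outcomes are compared by arm.

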## Discussion

A health care system aiming to reduce morbidity and mortality related to pregnancy must focus on maternal and newborn health. The World Health Organization recommended that “Ensuring skilled care for all women during pregnancy, childbirth, and the immediate postnatal period” is one of the strategies to reduce maternal and newborn mortality [23]. Methods described in this study could be a very innovative approach to implement GPC in existing selected facility and expected to have positive perinatal outcomes. Instead of providing usual care based on individual care, this group care at prenatal period will provide good understanding among mothers thus improvement of overall maternal and child health indicators is expected. Group care during pregnancy are proven to be useful in earlier studies that revealed group care ideally suited for mothers in developing countries and positive influence of GPC has been strongest for women with low socio-economic status [11, 12].

This study will compare birth and post partum outcomes for women who participated group prenatal care with women who received individual care. Results will be based on outcomes like increase utilization of prenatal and post natal care, institutional delivery, birth weight etc. Previous studies showed that Group prenatal care had statistically significant beneficial effects on gestational age and birth weight [24] and improve Utilization of postpartum family-planning services [25]. It is now imperative that we intend to experience this GPC approach on to exiting facility.

The study will contribute to improve maternal and newborn outcome in our existing health system. The intervention may improve the health well-being of both mother and child and the family as a whole. If successful, the project will scale up targeting more geographic areas and gradually cover both of the urban and rural areas for understanding the effectiveness of the group prenatal care. Findings of the research can be used for planning a new strategy and improving the health outcome for Bangladeshi women. Finally addressing the maternal health goal, this study is able to contribute to strengthening our health system.

## Abbreviations

ANC: Antenatal care
BCC: Behavioral Change Communication
ERC: Ethical Review Committee
GPC: Group prenatal care
icddr,b: International Centre for Diarrhoeal Disease Research, Bangladesh
LBW: Low-birth-weight
MCWC: Maternal & Child welfare Centre
MDG: Millennium Development Goal
MOHFW: Ministry of Health and Family Welfare
PNC: Post natal care
RRC: Research Review Committee
